## 4 ANALYSIS SETS/ POPULATIONS/SUBGROUPS

The analysis set consists of all 67 participants across all sites. Liver disease progression as measured using Fibroscan is defined as an increase in Fibroscan Stage (F1≤5.8 kPa (kiloPascals), F2 5.9-7.5 kPa, F3 7.6-9.3 kPa, F4>9.4 kPa) from baseline result to last study time point (either 36 months or last completed data point). These patients are referred to as “**progressors**”. Patients in the study are expected to show either no change, regression (decrease in Fibroscan Stage), or progression. Patients who do not show progression are referred to as “**non-progressors**”. Some participants’ fibrosis stage may fluctuate between first and last Fibroscan, such cases will be described but status will be defined only on first and last Fibroscan result. In addition, a pre-determined secondary definition of fibrosis progression was added, defined as 20% increase and ≥2 kPa (at least one value >5.9 kPa) [3].

Key subgroups of interest based on study entry characteristics include:

- HBeAg status at baseline (positive vs negative)
- Nadir CD4 cell count at baseline (>200 vs ≤200)
- CD4 nadir (%) (<10 or ≥10%)
- HIV viral load at CD4 nadir at baseline (>200,000 vs ≤ 200,000)
- ART duration (≤10 or >10 years)
- Derangement of ALT from normal range (yes vs no) – cut-offs are gender and site specific

Other exploratory subgroups (depending on numbers in each subgroup): gender (male vs female) and site (Bangkok vs others).

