| Treatment                                               | HBV-active agents (<2/2)                                                                                                                                                                                                                                    | Binary                                                                                 |
| Liver fibrosis                                          | Fibroscan stage (1/2/3/4)
Fibroscan score ( $\leq$ F2, >F2)                                                                                                                                                                                              | Categorical
Binary                                                                  |

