## 6 HANDLING OF MISSING VALUES AND OTHER DATA CONVENTIONS

Summary statistics (e.g., percentages) will be based on non-missing values. When applying the mixed model regression model, the underlying assumption on missing data is missingness at most at random.

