Correlations within and between endpoints at each visit and change from baseline visit will be explored (e.g., correlation sCD14 and Fibroscan score at month 12) and between consecutive follow-up visits and change from baseline visit separately (e.g., correlation sCD14 at month 12 with Fibroscan score at month 24). The Spearman correlation, exploring the degree to which the relationship between two outcomes is monotonic, will be used between two continuous outcomes and between an ordinal and continuous outcome, and point-biserial correlation between a binary and continuous outcome.

The following univariate models will be fitted to estimate the association between with the known risk factors (covariates) listed in Table 2 with each endpoint separately, both univariable (one covariate - unadjusted) and multivariable (more than one covariate - adjusted):

1. Univariate logistic regression model with the binary outcome of liver disease progression during the study (yes/no) adjusted for CD4+ T-cells at study entry (except for variables related to CD4).
2. Univariate mixed regression model with each outcome the repeated continuous outcome in microbial translocation/immune activation, hepatic inflammation, and Fibroscan score (kPa) adjusted for CD4+ T-cells at study entry (except for variables related to CD4).

In model 2 the functional form of time in the model will be explored (i.e., linear or curvilinear [e.g., quadratic, cubic]), a random intercept will be included in these models to represent a random effect for subject and the structure of the residual (within-patient) variance-covariance matrix will explored (e.g., unstructured, AR(1),...).

We will examine longitudinal liver stiffness measured by Fibroscan as a continuous variable in kPa and compare between those classified as progressors and non-progressors via univariate mixed regression.

### 7.1.2 Aim 2

Longitudinal plots by subgroup will be created of the microbial translocation/immune activation outcomes, hepatic inflammation outcomes, and liver disease outcomes. We will start by exploring subgroups in the univariate models outlined in Aim 1 by including appropriate interaction terms. It should be noted that the sample size will be a limiting factor in detecting statistically significant subgroup differences.

Analyses will be conducted using STATA, SPSS, or SAS.

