## 12 REFERENCES

1. Protocol (Version 7.0 dated 21 Jan 2016)
2. NHMRC project grant APP 1024406

## 13 CHANGES TO THE INITIAL FINAL VERSION 1

- Section 4 – Analysis Sets/Populations/Subgroups:

In addition to the primary definition of progressor, a pre-determined secondary definition of fibrosis progression was added, defined as 20% increase and  $\geq 2$  kPa (at least one value  $> 5.9$  kPa) as reported by Christiansen KM, Mossner BK, Hansen JF, Jarnbjer EF, Pedersen C, Christensen PB. Liver stiffness measurement among patients with chronic hepatitis B and C: results from a 5-year prospective study. PLoS One. 2014;9(11):e111912

The subgroup defined by derangement of AST from normal range was removed and the subgroups of CD4 nadir (%) ( $< 10$  or  $\geq 10\%$ ) and ART duration ( $\leq 10$  or  $> 10$  years) were added in order to manage low numbers (and group by meaningful cutoffs).

- Section 5 – Endpoints and Covariates:

Further markers of cell death (HMGB1) and immune mediators (tumour necrosis factor (TNF)- $\alpha$ , interleukin (IL)-10 and IL-18, chemokine (C-X-C motif) ligand (CXCL)-9, -10, -11, C-C motif chemokine ligand (CCL)2, CCL3, CCL4 and CCL5) were analysed. LPS was removed as an outcome. In addition, further covariates of interest (e.g., site) were examined.

- Section 7.1 – Statistical Procedures:

In addition to unadjusted models, adjusted models were fitted to account for differences in CD4+ T-cells at study entry (except for variables related to CD4). The analysis exploring correlation between two outcomes was removed due to the limitations to fit the proposed model in the data once available. As a result, no correlations or bivariate models were obtained. Statistical model 3 (mild vs severe Fibrosis over time) and model 4 (Fibrosis stage over time) were not fitted in favour of descriptively visualising the changes during the 3-year follow-up instead.

- Section 9 – Sample Size:

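### The adjusted models control only for CD4 at study entry, so in a cohort split 31 Bangkok / 36 Australia the planned associations are open to confounding by country

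*SAP*

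**What the plan says.** Section 7.1.1 plans to relate each covariate in Table 2 to each endpoint, "both univariable (one covariate - unadjusted) and multivariable (more than one covariate - adjusted"). The adjusted versions are then spelled out. Model 1 is a logistic regression of "liver disease progression during the study (yes/no) adjusted for CD4+ T-cells at study entry (except for variables related to CD4"). Model 2 is a mixed regression of the repeated continuous outcomes, including "Fibroscan score (kPa) adjusted for CD4+ T-cells at study entry (except for variables related to CD4"). Section 13 confirms that "adjusted models were fitted to account for differences in CD4+ T-cells at study entry". No other adjuster is listed.

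Site appears in three other places. Table 2 has Site/Country as a binary study-entry covariate. Section 4 has Bangkok versus others as an exploratory subgroup, if numbers allow. Section 13 says that "further covariates of interest (e.g., site) were examined". Baseline stiffness is likewise a Table 2 covariate, as "Fibroscan stage (1/2/3/4") and as a two-level score.

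Section 7.2 has confounders and heterogeneity in its title, but its text deals only with multiplicity and interpretation. Section 8 plans no sensitivity analyses. Section 6 assumes, for the mixed model, "missingness at most at random".

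**The concern.** The cohort comes from two countries in nearly equal parts. If a covariate such as time on ART, nadir CD4, BMI or ALT is distributed differently in Bangkok and Australia, and the endpoint also differs between them, a model without site attributes part of the country difference to the covariate. Estimating site's own effect, or a site interaction, does not remove site from the other associations; only including it alongside them does.

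The gap is widest for the CD4-related covariates, whose supposedly adjusted fit has no adjuster at all. It matters for interpretation because Section 7.2 asks for associations to be read by magnitude and direction, which is what confounding distorts.

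There is a second route. Missing at random is an assumption conditional on what the model contains. If loss to follow-up depends on country and country is not in the model, the assumption has to bear more weight than it needs to.

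**Working it through.** **1. Adjustment set, from Sections 7.1.1, 7.2, 8 and 13**

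| Covariate under study | Adjusters named, Model 1 | Adjusters named, Model 2 |
|---|---|---|
| Not CD4-related | CD4 at study entry | CD4 at study entry |
| CD4-related | none | none |

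The general phrase about more than one covariate is not expanded into any further list, and Sections 7.2 and 8 add nothing.

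**2. Cohort split, from Table 1.** Bangkok 31/67 = 46.3%; Australia 36/67 = 53.7%. Both agree with the printed figures.

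**3. Three-year follow-up by country, from Table 1**

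- Bangkok: 30/31 = 96.8%, so 1/31 = 3.2% lost.
- Australia from its three site rows: 14 + 8 + 6 = 28; 28/36 = 77.8%, so 8/36 = 22.2% lost.
- Australia from the printed subtotal: 24/36 = 66.7%, so 12/36 = 33.3% lost.

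Consistency check: 30 + 28 = 58, the printed overall total, whereas 30 + 24 = 54. The printed 41.3% matches 24/58 = 41.4% but for rounding, while 28/58 = 48.3%. The subtotal is therefore the figure that disagrees with the rest of the table. On the site rows, Fisher's exact test of 1/31 against 8/36 gives p = 0.03; using the printed subtotal would only widen the contrast.

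(In the same table, 20/67 for the Melbourne hospital site is 29.9%, not the printed 31.3%.)

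**4. Cost of adding site to each model**

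*Model 2.* One binary fixed effect is one degree of freedom, in 67 participants with up to four yearly measurements each.

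*Model 1.* Section 9 expects at least 8% to progress: 0.08 × 67 = 5.4 events. Events per parameter (excluding the intercept) are then:

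| Terms in the model | Calculation | Events per parameter |
|---|---|---|
| Covariate + CD4 | 5.4 / 2 | 2.7 |
| + site | 5.4 / 3 | 1.8 |
| + site + baseline stiffness | 5.4 / 4 | 1.3 |

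The SAP does not give the actual number of events. At an assumed 30% progression (20.1 events) the three rows become 10.0, 6.7 and 5.0. Site is cheap in Model 2 and expensive in Model 1 at the stated rate.

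**5. Size of the possible bias.** This cannot be computed from the SAP, which shows no covariate or endpoint by site. If site is unrelated to either the covariate or the endpoint, the confounding bias is nil.

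**The case against.** The strongest reply is that nothing in the SAP shows confounding. A reader might infer that the associations are confounded by site; the document supports only that they could be. A reader might also want a figure for a spurious marker odds ratio for progression. That would need invented site differences, and it would describe a regression the SAP does not specify: sCD14, CXCL10 and the other immune markers are endpoints in Table 2, while the models relate endpoints to the study-entry covariates. Both points stand.

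The ALT limits, of which Section 4 says "cut-offs are gender and site specific", might be read as evidence that patients differ between sites. They standardise the classification of ALT and do not show that.

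Site is not ignored, since it is examined as a covariate and possibly as a subgroup. That is true, but it does not adjust the other associations. Leaving CD4 out when the covariate is CD4-related is a reasonable way to avoid collinearity; the problem is that nothing else remains.

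On retention, losses within Australia also vary by site (6/20, 2/10, 0/6), so a two-country term captures only part of the pattern. Missing at random strictly needs site only if site predicts the missing values beyond the observed repeated measurements. Hence the claim is more credible, not valid or invalid.

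It is tempting to ask for baseline kPa in the models as well. In Model 2 with kPa as outcome, baseline is one of the repeated outcomes. In Model 1 a participant at F4 cannot rise a stage, so baseline does matter there. But progression is measured from that same error-prone scan, adjusting for it invites regression to the mean, and there are about 5 events to support it. It should not be required.

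**Conclusion.** The concern holds in a limited form. The only adjuster is CD4 at study entry, with none for CD4-related covariates, and no other section covers country. The planned associations are therefore open to confounding by country, to an unknown extent that may be nil. Country also appears to predict loss (3.2% against 22.2%), so the mixed model's missing-data assumption is more credible with site included. The retention contrast rests on the Australian site rows, which agree with the total of 58; the printed subtotal would make it larger, and the table needs reconciling either way. The case for change is clear in Model 2, where the cost is negligible. In Model 1 it supports only a sensitivity analysis, on the assumption that events are near the stated 8%.

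**What to change.** - **Model 2:** add Site/Country (Bangkok versus Australia) as a fixed effect in every adjusted fit, including those for CD4-related covariates, and report the unadjusted results alongside. Cost: one degree of freedom.
- **Model 1:** keep the planned fit as the main analysis and add site only in a sensitivity analysis by penalised likelihood (Firth). Penalisation stabilises the estimate but adds no information, so wide intervals should be expected. Do not require adjustment for baseline kPa. Section 8 would need to list this analysis.
- **Section 7.2:** state the adjustment set for each model and the reason for it, so that the text covers the confounders named in its heading.
- **Table 1:** reconcile the Australian three-year subtotal with its site rows and the overall total, and correct the percentage for 20/67.

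All of this is SAP wording plus refits using a variable already collected; no new data are needed.

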## 1 INTRODUCTION

In order to determine what drives liver disease progression in HIV-HBV co-infected patients, a group of 67 patients on suppressive HBV-active HAART were prospectively followed and changes in liver disease progression were measured over 3 years, with study visits every 6 months (baseline, 6, 12, 18, 24, 30, and 36 months of follow-up) [1, 2]. The schedule of assessments is listed in Appendix 1. Liver fibrosis (assessed by transient elastography) and peripheral blood mononuclear cells (PBMCs) were assessed at baseline then annually.

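### Comparing kPa over time between progressors and non-progressors by mixed regression is circular, because the same kPa readings define the groups

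*SAP*

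**What the plan says.** Section 4 of the SAP: "Liver disease progression as measured using Fibroscan is defined as an increase in Fibroscan Stage". The stages are bands of kPa: "F1≤5.8 kPa (kiloPascals), F2 5.9-7.5 kPa, F3 7.6-9.3 kPa, F4>9.4 kPa". If a participant's stage fluctuates in between, "status will be defined only on first and last Fibroscan result". The secondary definition needs a rise of 20% and of at least 2 kPa, so it too is computed from kPa.

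Section 7.1.1, after the two numbered models, plans to examine "longitudinal liver stiffness measured by Fibroscan as a continuous variable in kPa and compare between those classified as progressors and non-progressors", by mixed regression. It does not remove the classifying scans from the outcome, does not call the comparison descriptive, and does not say whether the tested term is the group main effect or group-by-time. Interaction terms are mentioned only in section 7.1.2, for the Aim 2 subgroups.

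Section 7.2 says that associations are interpreted from p-values, 95% confidence intervals, magnitude and direction. Section 8 plans no sensitivity analyses. Section 11 already lists a summary (3C1) and a plot (3C2) of the liver outcomes by progressor status.

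**The concern.** The predictor in this regression is computed from two of the outcome's own values. A participant whose last scan happens to read high, or whose first happens to read low, is more likely to be labelled a progressor. The same chance readings then appear as that group's rising trajectory. A significant difference would be expected even if no liver had changed, so the result says nothing about whether progressors are a real group.

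What is at stake is interpretation. A reported slope difference with a small p-value would look like independent support for the classification. The SAP expects at least 8% of patients to have increased stiffness (section 9), which is 0.08 × 67 = 5.4, or about 5 participants. With a group that small, how many are misclassified by scan error is an open question, and this model cannot answer it.

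**Working it through.** The SAP states no figure for this analysis, so there is none to reproduce.

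**Inputs from the SAP.** n = 67 (section 4: "The analysis set consists of all 67 participants across all sites"). Fibroscans "were assessed at baseline then annually" (section 1), so at months 0, 12, 24 and 36. Follow-up at 3 years is 58 of 67, so 67 − 58 = 9 stop earlier (Table 1). The model has a random intercept (section 7.1.1). The significance level is 5% (section 9).

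**Assumptions not in the SAP.** Log-normal kPa with median 5, 6 or 7; between-patient log SD 0.25 or 0.40 (0.35 in the fitted-model check and the controls); scan-to-scan coefficient of variation (CV) 5% to 25%, independent between visits; a two-sided test.

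**Step 1: how much of the slope comes from the classifying scans.** With four complete annual scans, the group-by-time estimate in a random-intercept model is the difference in mean least-squares slopes. With time centred at −1.5, −0.5, 0.5 and 1.5 years, the sum of squares is 5, and each participant's slope is

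slope = 0.3 × (y36 − y0) + 0.1 × (y24 − y12).

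For a stable liver with independent scan error of variance v, the slope variance is 0.09 × 2v + 0.01 × 2v = 0.20v. The first and last scans contribute 0.18v of this, or 90%. Progressor status is a function of those same two scans.

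**Step 2: simulation with no true change in anyone.** Each participant has a constant true kPa plus scan error, rounded to 0.1 kPa. Status is assigned by section 4, and the random-intercept model is fitted to the same four scans (2,000 studies per setting). A study with fewer than two progressors counts as not significant for group-by-time. Selected settings, primary definition, raw kPa:

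| Median kPa, between-patient log SD | Scan CV | Mean false progressors | Group-by-time significant | Main effect significant | Spurious slope difference (kPa/year) |
|---|---|---|---|---|---|
| 7, 0.40 | 5% | 5.1 | 68% | 0% | 0.22 |
| 7, 0.25 | 5% | 6.7 | 91% | 1.5% | 0.22 |
| 6, 0.40 | 10% | 8.6 | 97% | 6% | 0.43 |
| 6, 0.40 | 15% | 11.6 | 99% | 10% | 0.64 |
| 6, 0.40 | 20% | 13.6 | 99.8% | 11% | 0.84 |

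Over all settings:
- Group-by-time, CV 10-25%: 94-100% on raw kPa and 91-100% on log kPa. The spurious slope difference is about 0.4 to 1.2 kPa per year.
- Group-by-time, CV 5%, raw kPa: 67-91%.
- Group main effect: 0-77%, depending on the kPa distribution.
- Secondary definition, CV at least 10% and at least two progressors: group-by-time 99-100%.

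**Step 3: fitted mixed model with 9 of 67 stopping early, last available scan used (about 150 studies per setting).** At CV 10%, 15% and 20%, group-by-time is significant in 97%, 100% and 100%; with categorical time, 96%, 100% and 100%; the main effect, 14%, 19% and 17%.

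**Step 4: controls.** With group labels drawn at random, group-by-time is significant in 5.4% and the main effect in 4.6%. Using only the month 12 and 24 scans, group-by-time is significant in 5.2% (CV 15%) and 6.6% (CV 20%). The inflation therefore comes from reusing the first and last scans.

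**Step 5: how far the month 12-24 comparison can be trusted.** If scan errors follow AR(1) with unit variance and correlation r between adjacent visits, then

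cov(y24 − y12, y36 − y0) = r − r² − r² + r = 2r(1 − r).

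This is 0 only at r = 0 (or r = 1); at r = 0.3 it is 0.42. In simulation, the interior comparison rejected in about 11-23% of null studies at r = 0.3 and about 16-43% at r = 0.5.

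**The case against.** The best defence is that the sentence is minor. It is unnumbered, feeds no other model, and the SAP gives it no validating role. Aim 1 asks whether microbial translocation or inflammation predicts progression, which models 1 and 2 address. This stands, and it limits the severity. It does not rescue the test: an illustration of the definition needs no regression, and section 7.2 has p-values and intervals interpreted.

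Three stronger readings are tempting, and the SAP does not support them.

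- A reader might infer that the comparison is bound to be significant. That fits group-by-time at scan variation of 10% or more. Section 7.1.1 also allows a group main effect, which is often not significant, and the SAP gives no scan error from which to fix the rate.
- A reader might infer that Aim 1 as a whole is compromised. No Aim 1 conclusion is stated to depend on this comparison.
- A reader might extend the point to the correlations in outputs 4A and 4B. Sections 7.1.1 and 11 still list correlations, but section 13 says that none were obtained, and no pairing of progression status with kPa is named. That extension is not made here.

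**Conclusion.** The concern holds: the comparison is circular under both definitions of progression, and this follows from sections 4 and 7.1.1 without any numerical assumption. Its p-value, confidence interval and slope difference have no valid null.

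The size does depend on assumptions. For group-by-time, the false-positive rate is about 91-100% at scan variation of 10-25% and about 67-91% (raw kPa) at 5%. For a main effect it is 0-77%, so distorted in a direction that depends on the kPa distribution. Scan error, the kPa distribution and independence of errors between visits are all assumed. None of this shows that the observed progressors are false; it shows that this model cannot tell. It should be fixed, but it does not undermine the main Aim 1 models.

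**What to change.** In section 7.1.1, delete the mixed-regression comparison of kPa by progressor status. Show kPa by progressor status only descriptively, in outputs 3C1 and 3C2, with no p-value or confidence interval for the group difference, and state that the separation follows from the definition. If the model has already been run, treat its result the same way in reporting.

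If a check on the classification is wanted, one option is to take participants whose last scan is at month 36 and compare the month 12 to 24 change in kPa between the groups. The SAP should then say that this is valid only if scan errors are independent between visits, an assumption not to be taken for granted when section 7.1.1 itself lists AR(1) as a candidate residual structure. It should also say that this comparison has less power.

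The cost is a change of wording and one model fewer. No data are lost, and models 1 and 2 stay as they are.

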| Demographics                                            | Gender (male/female*)
(* TransGender Female categorised as Female)
Age (years)
Body Mass Index (kg/m  )
Site/Country                                                                                                                | Binary

Continuous
Continuous
Binary                                       |
| Adherence and alcohol questionnaires                    | Alcohol excess intake (yes/no)                                                                                                                                                                                                                              | Binary                                                                                 |
| CD4 nadir
CD4+
CD8+                               | Nadir CD4 cell count (cells/ $\mu$ L)
Nadir CD4 cell count (>200/ $\leq$ 200 cells/ $\mu$ L)
Nadir CD4 cells (%)
Nadir CD4 cells (<10/ $\geq$ 10%)
CD4+ T-cell count (cells/ $\mu$ L)
CD4+ T-cells (%)
CD8+ T-cell count (cells/ $\mu$ L) | Continuous
Binary
Continuous
Binary
Continuous
Continuous
Continuous |
| HIV RNA at time of CD4 nadir                            | HIV viral load at CD4 nadir (cps/mL)
HIV viral load at CD4 nadir (>200,000/ $\leq$ 200,000 cps/mL)                                                                                                                                                       | Continuous
Binary                                                                   |
| Hepatitis serology                                      | HBeAg status (positive/negative)
ALT (IU/mL)
ALT derangement from normal range (yes/no)                                                                                                                                                               | Binary
Continuous
Binary                                                         |
| HIV characteristics                                     | Duration of ART (>10/ $\leq$ 10 years)
Time on ART (years)                                                                                                                                                                                               | Binary
Continuous                                                                   |

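### The mixed-model comparison of kPa between progressors and non-progressors is circular, because the groups are defined by the same kPa readings; report it as description without a test

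*SAP*

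**What the plan says.** SAP section 4 defines the groups. Progression "is defined as an increase in Fibroscan Stage" from baseline to the last available time point, and the stages are bands of stiffness: "F1≤5.8 kPa (kiloPascals), F2 5.9-7.5 kPa, F3 7.6-9.3 kPa, F4>9.4 kPa". Fluctuation between the first and last scan is expected and will be described, but "status will be defined only on first and last Fibroscan result". The secondary definition combines a relative rise of 20% with an absolute rise of at least 2 kPa, so it too is computed from the readings. All patients who do not progress, including those whose stage falls, are non-progressors.

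Section 7.1.1 then makes serial stiffness, as a continuous measure, the outcome of a further analysis. The plan for it is to "compare between those classified as progressors and non-progressors via univariate mixed regression". It does not say whether the term of interest is status or status by time. Section 7.2 provides for p-values and 95% confidence intervals without multiplicity adjustment, and section 8 plans no sensitivity analyses. Summaries and plots of the liver outcomes by progressor status are listed separately in section 11 (outputs 3C1 and 3C2). The SAP contains no caveat that the groups are built from the outcome.

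On the minor point, section 7.1.1 relates the Table 2 covariates to each endpoint separately. Those covariates include entry ALT, ALT derangement, entry Fibroscan stage and the dichotomised Fibroscan score. The endpoints include ALT and kPa at four yearly visits, the first of which is study entry.

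**The concern.** Scans are taken at months 0, 12, 24 and 36. For a patient with complete follow-up, two of the four outcome values decide the group. Sorting patients on the rise from first to last value creates a difference in slope between the groups even if every rise and fall is measurement noise. A small p-value is then a product of the classification. Progression is the study's key outcome, so a reader could take such a p-value as confirming that progressors are a distinct group, when noise alone would give the same result.

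Model 2 has a milder form of the same problem. When entry ALT is the covariate and ALT the outcome, or entry stage the covariate and kPa the outcome, the entry reading stands on both sides and the association is inflated.

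**Working it through.** The SAP states no figure for this comparison, so there is none to reproduce.

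**Why the slope difference is built in.** Code the visits as 0, 1, 2 and 3 years. The centred times are -1.5, -0.5, 0.5 and 1.5, with sum of squares 5. A completer's least-squares slope is therefore

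0.3 × (month 36 − month 0) + 0.1 × (month 24 − month 12).

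With complete data and a random intercept, the group-by-time estimate is the difference between the groups' mean slopes. A rise in stage requires month 36 to exceed month 0, so the first and heavier term is positive for every progressor with complete data. Under the secondary definition it is at least 0.3 × 2 = 0.6 kPa per year. The non-progressors hold all the falls.

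**Simulation with no true change.**
- From the SAP: 67 patients; four annual scans; the section 4 cut-offs and secondary rule; 58 of 67 followed to 3 years, so 9/67 = 13.4% with an earlier last reading in the wide grid below; a random intercept (stated for model 2 and assumed to apply here).
- Assumed: log-normal stiffness, constant true level per patient, median 5.5-6.5 kPa, between-patient log-SD 0.25-0.40, within-patient log-SD 0.05-0.25 (close to the CV at these sizes).
- Models: kPa on time, status and time × status; and kPa on time and status only. Wald test at 0.05.

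Stage definition, median 5.8 kPa, between-patient log-SD 0.35 (120-300 cohorts per noise level):

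| Noise | False progressors of 67 | Time × status p<0.05 | Spurious slope difference, kPa/year | Status main effect p<0.05 |
|---|---|---|---|---|
| 5% | about 5 | 75-76% | not recorded | 6% |
| 10% | about 9 | 98-99% | 0.41-0.42 | 18% |
| 15% | about 12 | 99-100% | 0.63-0.64 | 28% |

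The ranges are over separate sets of runs. The main-effect column comes from one set of 120 cohorts per level.

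Over the wider grid (100-120 cohorts per setting):
- Stage definition, noise log-SD 0.10-0.25: on average 8-16 patients labelled progressors by noise alone; time × status significant in 96-100%; status main effect in 0-58%.
- Stage definition, noise log-SD 0.05, median 6.0: about 5 progressors; time × status significant in 80%.
- Secondary definition (seven settings, only runs with at least two progressors): time × status 99-100%; main effect 38-76%. At noise 0.10 only 13-47% of runs had two progressors, so those rates rest on few cohorts.
- Reference with randomly assigned labels: 2% of 200 cohorts, so the model does not inflate the error rate when the labels do not come from the outcome.
- Months 12 and 24 only: time × status significant in about 4-12%, close to nominal.

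**Model 2 with the entry value on both sides.** Take a continuous covariate equal to the entry value, constant variance, and the same correlation (ICC) between any two visits. The slope on the entry value is 1 at month 0 and ICC at each of months 12, 24 and 36. The pooled slope is (1 + 3 × ICC)/4 instead of ICC:
- ICC 0.5: (1 + 1.5)/4 = 0.625 instead of 0.50.
- ICC 0.8: (1 + 2.4)/4 = 0.85 instead of 0.80.

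The excess is (1 − ICC)/4. The ICC values are assumptions. The formula does not give the size for binary ALT derangement or categorical stage.

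**The case against.** The strongest reply is that the SAP never names a time × status term here, although section 7.1.2 does name interaction terms where it wants them. If only a status main effect is tested, rejection without true change falls to 6-28% in the table and 0-58% over the wider grid. This stands. A reader might infer that a significant result is nearly guaranteed under any analysis; the document does not support that, because it leaves the term open. It does not rescue the test, since the label comes from the outcome under either reading.

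A second reply is that the result depends on unstated noise, median and spread, and that a median near 5.8 kPa lies on the F1/F2 boundary. Also true. The inflation persists at medians of 5.5 and 6.5 kPa, and it weakens but remains large at 5% noise.

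A third reply is that the comparison is not empty. It shows how many kPa a stage change represents, which is useful when a move from 5.8 to 5.9 kPa is enough to change stage. Months 12 and 24 normally play no part in the labels of the 58 patients seen at 3 years. This stands too: it would be too strong to say that the analysis carries no information. The circular part is the test that uses all visits.

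Finally, section 7.1.1 speaks only of examining and comparing, and section 7.2 asks for interpretation by magnitude and direction as well as p-values. That the result would be presented as proof of distinct trajectories is therefore a possible use, not a stated one. But magnitude and direction are distorted by the same selection, so that instruction gives no protection.

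On model 2, a reader might see an inconsistency with the exception made for CD4-related variables. It is not a parallel rule: it governs adjustment for CD4, not a covariate that overlaps its own outcome.

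**Conclusion.** The comparison is wrong as planned inference. Under the group-by-time reading it yields p<0.05 in about 96-100% of no-change cohorts at 10-15% noise and about 70-80% at 5% noise, with a spurious slope difference of roughly 0.4 to 0.7 kPa per year at 10-15% noise. These figures rest on assumed noise, median and spread; the circularity itself follows from the definitions alone. A main effect of status rejects less often, and the SAP should say which term it means.

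The fault is confined to this comparison. A reader might infer that it undermines Aim 1 as a whole; it does not, because the models of markers and other covariates that are not derived from Fibroscan do not depend on it.

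The overlap in model 2 is real but minor: a slope excess of 0.125 at ICC 0.5 and 0.05 at ICC 0.8 for a continuous covariate.

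**What to change.** In section 7.1.1, replace the mixed-model comparison of kPa by progressor status with a descriptive presentation through outputs 3C1 and 3C2, giving estimates without p-values. State that the groups are defined by the same Fibroscan readings under both definitions, and that the comparison will not be cited as evidence of distinct trajectories.

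In model 2, when the covariate is the entry value of the outcome itself (entry ALT or ALT derangement for ALT; entry Fibroscan stage or score for kPa), use only months 12, 24 and 36 as outcome. Entry ALT will still predict later ALT, with slope equal to the ICC, but that is genuine persistence over time.

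The cost is a change of wording, one test dropped, and a few models refitted without the baseline visit. No new data are needed. Section 13 describes some models as already fitted; if this comparison is among them, the change applies to how it is reported.
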